## Summary

The maintenance of the deciduous tooth until its physiological exfoliation occurs is one of the main objectives of pediatric dentistry. Endodontic treatment in deciduous teeth resulting from carious or traumatic lesions with pulpal involvement is often necessary and we often find it difficult to perform it, due to the difficult control of the child, the internal anatomy of the root canals, and root resorptions. The non-instrumented endodontic treatment technique (NIET) associated with antimicrobial drugs has advantages such as shorter chair time and less complexity than the conventional technique in which root canal instrumentation is performed. The aim of this study is to carry out a controlled and randomized clinical trial to compare the effectiveness of non-instrumented endodontic treatment (NIET) in primary teeth associated with the use of two obturator pastes. 120 necrotic deciduous teeth of children aged between 3 and 6 years will be selected; and the teeth will be divided into two groups. In Group 1 and Group 2, the root canals will not be instrumented, just irrigated and filled with the respective pastes, CTZ and Guedes-Pinto. The radiographic aspects will be evaluated, considering the repair process, clinically will be evaluated: presence of fistula and mobility, the evaluations will be carried out in both groups on the day of treatment and in periods of 1, 3 and 6 months after treatment. For the main outcome, the tooth will be the unit of analysis and the Kaplan-Meier test will be performed to estimate the survival rates of the included teeth. For comparison between the two groups, Student's t test or Mann-Whitney test will be performed, depending on the normality of the data. In addition, Poisson regression analyzes will be carried out, in order to allow the evaluation of the influence of some variables on the results. For all analyses, the significance value will be adjusted to 5%.

**Key words:**Endodontic treatment, Primary teeth, Guedes-Pinto paste, pulp necrosis, NIET, CTZ.

## **1. Introduction**

Research points to a decrease in dental caries in the primary dentition worldwide, despite this, the prevalence of caries remains high in some population groups. Childhood caries is still very common, it can cause severe destruction and quickly reach the dental pulp.

The main causes of inflammation and pulpal necrosis in deciduous teeth are carious and traumatic injuries. The occurrence of caries in the deciduous dentition is quite significant, with approximately 75% of teeth with deep caries having pulp involvement. Once the condition of pulp is established, irreversibility of pulpal inflammation, or tissue necrosis, radical endodontic treatment should be performed. There are 2 treatment options for deciduous teeth with infected and/or necrotic pulp: extraction or pulpectomy.

Pulpectomy consists of the complete removal of necrotic cells and irreversibly infected pulp from an affected tooth, so that the tooth remains asymptomatic and functional in the oral cavity until it exfoliates normally. Premature loss of deciduous teeth can produce changes in the tooth eruption guide permanent, which can lead to phonetic disorders and harmful oral habits, such as tongue interposition and aesthetic consequences.

Pulp therapy in deciduous teeth is a complex treatment, mainly due to instrumentation procedures, complexity of the apical delta, biological cycle of deciduous teeth, physiological root resorption and rhizolysis, and long treatment sessions during which the child sometimes does not always cooperate.

The most used technique for endodontic treatment in deciduous teeth is performed with manual files and disinfectant irrigating solutions. Mechanical instrumentation associated with chemical irrigation does not completely eliminate microorganisms present in the root canal. Thus, the objective of endodontic treatment is maximum disinfection of the root canal system (RCS) and prevention of reinfection.

The technique called Lesion sterilization and tissue repair therapy (LSTR) was proposed for non-vital deciduous teeth, with advanced root resorption, strategically important teeth, with bone loss, mobility, radiolucency in the furcation area, uncooperative patients who cannot undergo extraction at that time. This technique, however, is contraindicated for patients allergic to any of the components of the antibiotic agents used, extensive internal or external resorption, teeth close to exfoliation, perforation of the pulp floor and children with bacterial endocarditis. The combination

of drugs is used to minimize the amount of microorganisms present in the lesion or in the root canal and tissue repair is expected if the lesion is disinfected. When applied to treat necrotic pulps in deciduous teeth, it is performed without instrumenting the root canals, that is, without conventional chemical-mechanical preparation and an association of antimicrobials is deposited in the entrances of the root canals. The LSTR approach or non-instrumental endodontic treatment (NIET) therefore involves the use of an association of antimicrobial drugs and has advantages such as less time, less complexity, prevention of irritation of the periapical tissues and the germ of the permanent successor, in addition to being able to be used in deciduous teeth that present a rhizolysis process of up to more than a third of the roots. without the conventional chemical-mechanical preparation and an association of antimicrobials is deposited in the entrances of the root canals. The LSTR approach or non-instrumental endodontic treatment (NIET) therefore involves the use of an association of antimicrobial drugs and has advantages such as less time, less complexity, prevention of irritation of the periapical tissues and the germ of the permanent successor, in addition to being able to be used in deciduous teeth that present a rhizolysis process of up to more than a third of the roots. without the conventional chemical-mechanical preparation and an association of antimicrobials is deposited in the entrances of the root canals. The LSTR approach or non-instrumental endodontic treatment (NIET) therefore involves the use of an association of antimicrobial drugs and has advantages such as less time, less complexity, prevention of irritation of the periapical tissues and the germ of the permanent successor, in addition to being able to be used in deciduous teeth that present a rhizolysis process of up to more than a third of the roots.

The filling materials for deciduous teeth must have the following properties: resorbable, radiopaque, bactericidal, promote adequate filling and adherence to the walls of the root canals, easily removed when necessary; in addition to not causing damage to the periapical tissues and to the permanent tooth germ, nor altering the color of dental structures. However, there is no single material that fulfills all the desirable requirements for a filling material, in addition to there being no consensus in the literature about the best material to be used in the endodontics of deciduous teeth.

Among the filling materials for deciduous teeth, we have the Guedes Pinto paste and the CTZ antibiotic paste. The Guedes-Pinto paste is composed of iodoform, camphorated paramonochlorophenol and an association of corticoid and antibiotic (Rifocort) and has been widely used due to its antimicrobial and antiseptic properties, in addition to being

radiopaque and resorbable, thus, it does not harm the process of rhizolysis of the deciduous tooth and the eruption of the permanent successor. The CTZ antibiotic paste, on the other hand, is composed of chloramphenicol, tetracycline and eugenol zinc oxide has been especially indicated in public health services and in cases of patients who are not cooperative. It presents easy manipulation, biological compatibility; however, there are still controversies regarding the safety of using chloramphenicol. 

The success of endodontic treatment is directly related to intracanal bacterial decontamination and there is a difficulty in endodontic treatment in deciduous teeth, often due to difficult child control, internal anatomy of root canals, and root resorption. Considering these factors, it becomes necessary to know the effectiveness of non-instrumented endodontic treatment (NIET) in deciduous teeth associated with the use of two filling pastes. Therefore, carrying out this clinical study to evaluate the effectiveness of non-instrumental endodontic treatment in deciduous teeth, comparing the performance of CTZ paste and Guedes-Pinto paste, will support the analysis for choosing the most appropriate protocol.

## **2. METHODS**

### **2.1 Main goal**

The aim of this study is to carry out a controlled and randomized clinical trial to evaluate the effectiveness of endodontic treatment non-instrumental (NIET) in deciduous teeth with CTZ paste (antibiotic-based paste) compared with the effectiveness of Guedes-Pinto Paste (iodoform-based paste).

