### **2.2 Experimental Design**

The present work is characterized as a controlled and randomized clinical trial of non-inferiority, with two parallel arms and allocation rate of 1:1 and which will be carried out at the Dental Clinic of the Metropolitan University of Santos (UNIMES). Because it is a randomized clinical trial and seeking greater transparency and quality of this research, we will use the CONSORT recommendations (Consolidated Standards of Reporting Trials). The study protocol was registered on the international platform of clinical trials ClinicalTrials.gov, with registration number NCT04587089

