### 2.4 Determination of sample size

To carry out the sample calculation, a 12-month success rate for the CTZ paste of 86.4% was assumed. The non-inferiority limit was considered as 15%, power of 80% and significance level of 5%, which resulted in 38 teeth per group. 20% were added to this number due to possible sample losses and 40% due to the patient having more than one tooth included, resulting in a sample of 60 deciduous anterior teeth per group, totaling 120 deciduous anterior teeth.

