### 3. Expected Results

Through the present work, we will be able to assess whether there will be a difference in effectiveness between the proposed treatments, as well as whether Guedes-Pinto paste in the NIET technique will present equal or better clinical and radiographic results when compared to the CTZ paste.

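### The protocol declares non-inferiority but never names the test and reference paste, and its main goal and expected results point in opposite directions

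*Protocol*

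**What the plan says.** - **Design (2.2).** The trial is a "controlled and randomized clinical trial of non-inferiority, with two parallel arms and allocation rate of 1:1". The section does not say which paste is to be shown non-inferior to which.
- **Main goal (2.1).** Treatment is evaluated "with CTZ paste (antibiotic-based paste) compared with the effectiveness of Guedes-Pinto Paste (iodoform-based paste". Read as a directional statement, CTZ is under test and Guedes-Pinto is the comparator.
- **Expected results (3).** The trial will show "whether Guedes-Pinto paste in the NIET technique will present equal or better clinical and radiographic results when compared to the CTZ paste". Here Guedes-Pinto is under test and CTZ is the comparator. The same sentence also speaks of a difference in effectiveness, which has no direction.
- **Sample size (2.4).** The calculation assumes "a 12-month success rate for the CTZ paste of 86.4" per cent and continues: "The non-inferiority limit was considered as 15%, power of 80% and significance level of 5%, which resulted in 38 teeth per group". No rate is given for Guedes-Pinto, and CTZ is not called reference or test. After inflation the total is "resulting in a sample of 60 deciduous anterior teeth per group, totaling 120 deciduous anterior teeth".
- **Elsewhere.** Section 2.6 labels the arms G1 and G2 only. Section 2.10 names between-group tests without a direction.

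**The concern.** A superiority comparison with a two-sided test is symmetric, so the order in which two treatments are named does not matter. A non-inferiority comparison is not symmetric. Showing that Guedes-Pinto is less than 15 points worse than CTZ is a different result from showing that CTZ is less than 15 points worse than Guedes-Pinto, and one data set can support the first and not the second.

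The direction is the trial's objective, so it is not a detail that a protocol would normally leave to an analysis plan. An analysis plan that followed section 2.1 would depart from section 3, and the reverse. While the direction is open, whoever reports the trial can headline the direction that came out well and leave the other unmentioned.

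**Working it through.** **1. Does the sample size settle the direction?** Inputs from section 2.4: CTZ success 0.864, limit 0.15 (taken as absolute points), power 80%, alpha 5% (sidedness not stated), stated result 38 per group. The usual formula is

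n = [p_T(1 − p_T) + p_R(1 − p_R)] × (z_α + z_β)² / (0.15 + p_T − p_R)², with T the test and R the reference paste.

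- Both pastes at 0.864, one-sided 5%: 2 × 0.864 × 0.136 × (1.645 + 0.842)² / 0.15² = 64.6, so 65 per group. One-sided 2.5% gives 82 and one-sided 10% gives 48. The stated 38 is not reproduced.
- CTZ as reference at 0.864 and Guedes-Pinto as test at 0.90 (one-sided 5%): 38.
- CTZ as test at 0.864 and Guedes-Pinto as reference at 0.80 (one-sided 5%): 38.

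The 0.90 and 0.80 are not in the protocol. They show only that 38 can be reached with CTZ in either role, so section 2.4 does not fix the direction. That 38 does not follow from the stated inputs is a separate matter.

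**2. Why the paste that looks better tends to pass.** At 60 per group and 0.864 in both arms, SE = √(2 × 0.864 × 0.136 / 60) = 0.0626. The distance from the estimate to its confidence limit is 1.645 × 0.0626 = 0.103, or 1.96 × 0.0626 = 0.123. Both are below 0.15. If the observed difference favours a paste, its lower limit is therefore normally above −0.15.

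**3. How often the two readings disagree.** Exact binomial enumeration, Wald limits for the difference, 15-point absolute limit, teeth independent, both pastes at 86.4%:

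| n per group | One-sided alpha | Each fixed direction passes | Both pass | At least one passes | Opposite verdicts (at least one − both) |
|---|---|---|---|---|---|
| 60 | 5% | 78.7% | 57.4% | 100.0% | 42.6% |
| 60 | 2.5% | 68.1% | 36.3% | 100.0% | 63.7% |
| 34 | 5% | 56.0% | 15.1% | 96.9% | 81.8% |
| 34 | 2.5% | 45.2% | 4.6% | 85.8% | 81.2% |

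The 34 is illustrative. It applies the plan's own allowances in reverse: 60 / 1.4 = 43 for several teeth per child, then 43 × 0.8 = 34 for losses.

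**4. A lower success rate.** With both pastes at 70% and 60 per group, at least one direction passes in 100.0% (one-sided 5%) or 87.3% (one-sided 2.5%) of trials.

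**5. Error rate of a named claim.** With Guedes-Pinto at 71.4% and CTZ at 86.4% (exactly 15 points worse), 60 per group:

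| One-sided alpha | Guedes-Pinto non-inferior to CTZ (false) | CTZ non-inferior to Guedes-Pinto (true) |
|---|---|---|
| 5% | 5.5% | 99.3% |
| 2.5% | 2.7% | 98.4% |

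**The case against.** The strongest reply is that section 2.1 is a neutral comparison whose word order should not be over-read. It contains no non-inferiority term, and the Summary and Introduction state the aim symmetrically. On that view only section 3 is directional, and the usual reading of a rate quoted in a non-inferiority sample size, as the reference rate, would make section 2.4 agree with it. This has some force: the intended direction may well be Guedes-Pinto against CTZ. But it has to be inferred. Section 2.4 gives CTZ no role, the formal design statement in 2.2 names no direction, and the main goal, where a reader looks first, puts CTZ under evaluation.

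A reader might also infer that, because one direction or the other nearly always passes, a non-inferiority claim from this trial would be empty or its type I error inflated. The figures do not support that. The two nulls (15 points or more worse, 15 points or more better) cannot both be true, so at most one of the two claims can be false, and it passes at about the nominal rate: 5.5% or 2.7%. The 99.3% is power for a true claim. A claim that names its paste remains a valid one-sided statement. What remains is an undefined question and selective reporting.

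Finally, section 2.10 does not set out a margin test, so the percentages describe the limit-based analysis that the design implies, not one the protocol specifies.

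**Conclusion.** The point holds as a gap in the primary hypothesis. The protocol fixes a design and a limit that need a direction, states no direction, and orders the pastes in opposite ways in 2.1 and 3. At 60 independent teeth per group, with both pastes at 86.4% and an absolute 15-point limit, the choice of reading changes the verdict in about 43% (one-sided 5%) to 64% (one-sided 2.5%) of trials. The share in which at least one direction passes depends on the inputs: essentially all trials at those values, about 86 to 97% at an effective 34 per group, and 87% at 70% success with 60 per group and one-sided 2.5%.

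It would go too far to say that the sample size makes CTZ the reference, since 2.4 only assumes a CTZ rate, or that the open direction raises the false-positive rate of a named claim.

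**What to change.** Before any outcome data are seen, name one test and one reference paste and state a single hypothesis in the same terms in 2.1, 2.2, 2.4 and 3. Taking CTZ as reference is the smallest change, because it fits section 3 and the usual reading of 2.4:

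H0: success(Guedes-Pinto) − success(CTZ) ≤ −15 percentage points.

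Only this contrast should carry a non-inferiority claim; the reverse contrast is reported as descriptive. If the sponsor intends the other direction, 2.4 and 3 should be reworded to match. What matters is that one direction is chosen in advance.

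The cost is wording in four sections and giving up the reverse claim. The chosen direction has about 79% power (one-sided 5%) or 68% (one-sided 2.5%) at 60 independent teeth per group if both pastes succeed in 86.4%, against the 80% planned. The protocol should disclose this, and that power is lower once losses and several teeth per child are taken into account.

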### **2.2 Experimental Design**

The present work is characterized as a controlled and randomized clinical trial of non-inferiority, with two parallel arms and allocation rate of 1:1 and which will be carried out at the Dental Clinic of the Metropolitan University of Santos (UNIMES). Because it is a randomized clinical trial and seeking greater transparency and quality of this research, we will use the CONSORT recommendations (Consolidated Standards of Reporting Trials). The study protocol was registered on the international platform of clinical trials ClinicalTrials.gov, with registration number NCT04587089

### 2.3 Ethical aspects

The study will be conducted ethically according to the criteria described in the Declaration of Helsinki (World Medical Association Declaration of Helsinki, 2008). The protocol for this study will be submitted for approval by the Research Ethics Committee of the Metropolitan University of Santos (UNIMES). All information will be present in the free and informed consent form (Resolution no. 196 of the National Health Council, Ministry of Health, Federal District, Brazil, 03/10/1996), which will be signed in two copies, one belonging to the responsible, and another to the researchers.

Study participants will also be instructed that they may withdraw from the study at any time, for any reason, if they so choose. Researchers will also be able to remove participants from the study if they deem it necessary.

### 2.4 Determination of sample size

To carry out the sample calculation, a 12-month success rate for the CTZ paste of 86.4% was assumed. The non-inferiority limit was considered as 15%, power of 80% and significance level of 5%, which resulted in 38 teeth per group. 20% were added to this number due to possible sample losses and 40% due to the patient having more than one tooth included, resulting in a sample of 60 deciduous anterior teeth per group, totaling 120 deciduous anterior teeth.

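### The 38 teeth per group in section 2.4 do not follow from the stated inputs: with equal true success rates, 65 or 82 are needed and the planned 60 fall short of 80% power

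*Protocol*

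**What the plan says.** Protocol section 2.2 describes a "controlled and randomized clinical trial of non-inferiority" with "two parallel arms and allocation rate of 1:1". Section 2.4 assumes "a 12-month success rate for the CTZ paste of 86.4" per cent, taken from a cited trial, and continues: "The non-inferiority limit was considered as 15%, power of 80% and significance level of 5%, which resulted in 38 teeth per group". It then enlarges this figure: "20% were added to this number due to possible sample losses and 40% due to the patient having more than one tooth included". The outcome is given as 60 per group, or 120 teeth in all.

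Section 2.4 gives no success rate for Guedes-Pinto paste. It does not say whether the 5% is one-sided or two-sided, whether the 15% is absolute or relative, or which formula was used. The only hint about the second arm is in section 3, which asks whether "Guedes-Pinto paste in the NIET technique will present equal or better clinical and radiographic results" compared with CTZ.

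**The concern.** A sample-size statement should be reproducible from the inputs printed beside it. Here the base number is roughly half of what those inputs require under the ordinary assumption that the two pastes are equally good. The later increase to 60 does not offer spare sample, because section 2.4 assigns the extra teeth to losses and to children who contribute several teeth.

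At stake is how a failed non-inferiority result would be read. If the pastes are truly equal and the real power is well below the stated 80%, an inconclusive result is fairly likely. A reader who trusts the 80% would then take it as evidence against Guedes-Pinto.

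**Working it through.** **Inputs.** From section 2.4: CTZ success 0.864, margin 0.15, power 0.80, significance level 0.05. From section 2.2: two arms, 1:1, non-inferiority. Assumed because the protocol is silent: Guedes-Pinto success 0.864, margin absolute, teeth independent. Both readings of the 5% are shown: one-sided 5%, and one-sided 2.5% (a two-sided 95% interval).

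**Attempt to reproduce 38.** The standard unpooled formula is

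n per group = (z_alpha + z_power)² × [p1(1 − p1) + p2(1 − p2)] / margin²

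The variance term is 2 × 0.864 × 0.136 = 0.2350, and margin² = 0.0225.

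- One-sided 5%: (1.645 + 0.842)² = 6.183, and 6.183 × 0.2350 / 0.0225 = 64.6, so **65**.
- One-sided 2.5%: (1.960 + 0.842)² = 7.849, and 7.849 × 0.2350 / 0.0225 = 82.0, so **82**.

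Neither is 38. Other methods at the same inputs do not reach it either (one-sided 5% / 2.5%): Farrington-Manning 70 / 89, margin read as relative 87 / 110, arcsine 89 / 113, log odds ratio 121 / 154, equivalence 90 / 110. Single-arm formulas, which would not fit this design, come nearest at 33 and 41.

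**Power at equal true rates.** Power = Φ(0.15 / √(0.2350 / n) − z_alpha).

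| Teeth per group | 0.15 / √(0.2350/n) | One-sided 5% | One-sided 2.5% |
|---|---|---|---|
| 38 (stated base) | 1.907 | 60% | 48% |
| 48 (60 × 0.8, after the planned loss) | 2.144 | 69% | 57% |
| 60 (no loss) | 2.397 | 77% | 67% |

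Exact binomial enumeration at 60 teeth, over three common tests, gives 76.2% to 78.7% and 63.4% to 68.1%. The shortfall is therefore not an artefact of the normal approximation.

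The margin that 38 teeth support at 80% power is √(6.183 × 0.2350 / 38) = 19.6 points, or √(7.849 × 0.2350 / 38) = 22.0 points, not 15.

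**What would give 38.** Let Guedes-Pinto be truly better, so that the distance to the margin grows to 0.15 + (p2 − 0.864).

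- p2 = 0.90, one-sided 5%: variance 0.1175 + 0.0900 = 0.2075, distance 0.186, and 6.183 × 0.2075 / 0.186² = 37.1, so 38.
- p2 = 0.915, one-sided 2.5%: variance 0.1175 + 0.0778 = 0.1953, distance 0.201, and 7.849 × 0.1953 / 0.201² = 37.9, so 38.

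A common true rate of about 92.6% in both arms also gives 38 at one-sided 5%, but that contradicts the stated 86.4%.

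**The increase to 60.** Adding both percentages to the base gives 38 × (1 + 0.20 + 0.40) = 38 × 1.6 = 60.8, stated as 60. This step reproduces to within one tooth.

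**The case against.** The strongest reply is that equal rates is the reader's input, not the protocol's. Section 2.4 gives a rate for CTZ only, and section 3 allows that Guedes-Pinto may be better. With a true Guedes-Pinto rate of 90%, 48 evaluable independent teeth give 88% power at one-sided 5% and 81% at one-sided 2.5%. Even 86.9% would bring 60 independent, fully evaluable teeth to 80% at one-sided 5%. This stands as a limit on the conclusion. A reader might infer that 60 teeth per group cannot deliver 80% power whatever is assumed, and that is not so. But it does not rescue section 2.4: no such rate is printed or justified, and section 3's expectation includes equality, the case in which power falls short.

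A reader might also infer that the inflation step is a second arithmetic error. The text says the percentages were added to the base number, and done that way the result agrees to within a tooth. Dividing by (1 − loss) would be more accurate (38 / 0.8 = 47.5, against 38 × 1.2 = 45.6 for the loss allowance alone), but this is a secondary refinement.

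Finally, it is tempting to divide the 48 evaluable teeth by 1.4 and report a still lower power. The documents do not support that. The protocol gives neither an intracluster correlation nor a number of teeth per child, and section 2.7 randomises each tooth. One child may therefore have teeth in both arms, and positive within-child correlation can then reduce the variance of the difference between arms. The 40% allowance cannot be treated as a known design effect.

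Nor can the point be left to a statistical analysis plan: the protocol itself prints the inputs, the result and the power, and they do not agree.

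**Conclusion.** The point holds in this form: 38 teeth per group is not derivable from the inputs stated in section 2.4. Under equal true rates of 86.4% and an absolute 15-point margin, the base number is 65 (one-sided 5%) or 82 (one-sided 2.5%), so the stated 38 is 58% or 46% of it.

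The figures to lead with are 69% and 57% power at 48 evaluable teeth per group. If the pastes are truly equal, that is about a 31% or 43% chance of not concluding non-inferiority, against the 20% implied by the protocol. In the most favourable equal-rates case (one-sided 5%, all 60 teeth evaluable) power is 77%, a near miss. All these figures treat teeth as independent.

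The 65 and 82 are conditional on equal rates, because sidedness, the second rate and the formula are unstated. What is certain is that the calculation as printed cannot be reproduced and must be restated.

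**What to change.** Rewrite section 2.4 to state:

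- whether the 5% is one-sided or two-sided;
- the assumed true success rate in each arm;
- whether the 15% margin is absolute;
- the formula or software used.

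Then recompute the base number (65 or 82 under equal rates) and take one of these routes:

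1. **Keep 120 teeth** if feasibility fixes that number, and replace the 80% with the power delivered: about 69% or 57% with 48 evaluable independent teeth per group under equal rates.
2. **Declare an assumed advantage** if 38 came from one, giving the Guedes-Pinto rate and its justification.
3. **Enlarge the trial.** With the protocol's own additive allowances, 65 × 1.6 = 104 or 82 × 1.6 = 131.2, so 132 teeth per group (208 or 264 in total).

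While the section is open, apply the loss allowance as n / (1 − loss), and justify the allowance for several teeth per child in light of tooth-level randomisation.

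Routes 1 and 2 cost only wording and need no extra children, although route 1 makes the stated power less favourable. Only route 3 needs more recruitment.
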